### Study design

2.3

This study is designed as a prospective, double-blind, placebo-controlled, randomized parallel-group study that will be completed at Trinity College Dublin, Ireland. A total of 100 individuals with amnestic mild cognitive impairment (aMCI) based on diagnostic criteria described by the National Institute on Aging and Alzheimer's Association [17] will be recruited from Alzheimer's Ireland. Subject will receive a (real or control) non-invasive transcutaneous electrical stimulation of the greater occipital nerve (NITESGON) procedure. After providing written informed consent, subjects will be assigned to one of four groups. One group will receive active NITESGON, while the three groups will be control groups. One group will receive sham NITESGON (inactive control), while a second group will receive active NITESGON with local anesthesia (active control; local nerve anesthesia group) and a third group will stimulate the C5/C6 nerve (active control; same sensation different nerve). We will include three control groups so that we are able to verify that the effect is real, location specific and cannot be associated to a sensation effect.

We have opted to use a parallel-group design as it is unclear what the carry-over effect and/or wash-out period will be for NITESGON. Subjects will be randomized after screening evaluation and will be assigned to receive one of the four possible types of NITESGON. To eliminate subjective bias, all subjects and the investigator testing the endpoint measures will be blinded to the type of intervention. The researcher who will control the NITESGON device will not be involved in instructing the participant; this will be performed by a second researcher who will be blind to the stimulation protocol. The primary outcome will be change in memory performance as measured by a word association task, measured at baseline (T0), 7 days after NITESGON (T1) and after 28 (T2) days after NITESGON. Secondary outcomes include changes in resting EEG, which will be assessed immediately before and after NITESGON (see Fig. 1 and Table 1).

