*Inclusion Criteria*. One-hundred individuals, 50 years of age and above with amnestic mild cognitive impairment (aMCI) will be recruited. Participants who meet the following criteria will be eligible to participate: (1) Diagnosis of probable aMCI; (2) Montreal Cognitive Assessment between 18 and 25; (3) stable medication condition for more than 3 months; (4) stable medical condition for more than 6 months; (5) adequate visual and auditory acuity to complete neuropsychological testing; (6) capacity to provide written and dated informed consent form. Prospective participants, who meet the criteria, will be sent an electronic copy of the consent form. Participants will only be asked to sign the consent form at the site after going over the form with the researcher where all aspects of the study protocol will be reviewed.

*Exclusion criteria*. Participants will be deemed ineligible if they meet any of the following criteria: (1) any cause of cognitive decline or dementia that is not Alzheimer's disease related; (2) enrollment in any investigational drug study; (3) history in the past 2 years of epileptic seizures (participants with epilepsy who have been stable off medication or seizure free for 2 years may be included); (4) any major psychiatric disorder (a clinical diagnosis of major depressive disorder, bipolar disorder, or schizophrenia); (5) past history or MRI evidence of brain damage, including significant trauma, stroke, hydrocephalus, intellectual disability, or serious neurological disorder; (6) significant history of alcoholism or drug abuse of non-prescription drugs within the last 10 years; (7) familiarity with Swahili/Arabic language or Swahili culture due to the nature of the stimuli; (8) MCI due to vascular disease. Participants will be invited to complete MRI brain scans. Participants with pacemakers or other medical metal devices that are incompatible with MRI will not be eligible for MRI scanning as per standard procedures.

*Withdrawal of participants.* The investigator can decide to withdraw a subject from the study for urgent medical reasons. Subjects can leave the study at any time for any reason if they wish to do so without any consequences.

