### Study procedure

2.5

We will conduct this study as follows:(1)Screening of individuals with aMCI.(2)Randomly assigning aMCI subjects to one of the four NITESGON groups.(3)Administering one session of 1.5-mA active (*n* = 25) or control (*n* = 25 in each of three control group) NITESGON paired with a word-association task; administered by research assistant.(4)Behavioral assessments after each of the three blocks of studying the word associations and neural measures immediately after the last session of Behavioral assessments (T0).(5)Behavioral assessments at seven (T1) and 28 (T2) days after NITESGON.

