#### Secondary outcome measures

2.7.2

(1)Neurophysiology. Rest-state EEG will be collected immediately before and after NITESGON (T0) and will be correlated with the recall of the word-association task 7 (T1) and 28 (T2) days after NITESGON.(2)TES Adverse events*.* We will use the NITESGON exit questionnaire developed by Brunoni et al. [21] to assess potential side-effect (headache, neck pain, scalp pain, tingling, itching, burning sensation, skin redness, sleepiness, trouble concentrating, mood changes) at the end of T0.(3)Blinding. At the end of the experiment (T2), subjects will be asked if they thought they were assigned to the control or active group.(4)Control assessments. We will collect the California Verbal Learning Test II, Delis Kaplan Color Word Interference Test, Beck Depression (BDI) and Anxiety Inventory (BAI), Trial A & B, COWAT and DIGIT Span to verify that the effect obtained cannot be associated due to differences between groups on these control measures. These will be collected during visit 1 before NITESGON (T0), and 28 days after NITESGON (T2).

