*TES Adverse events.* A comparison will be conducted between the active and sham group using a one-way ANOVA with stimulation (active NITESGON vs sham NITESGON) as independent variable and adverse events as dependent variable.

*Blinding.* A Chi-square test will be conducted comparing actual stimulation (active NITESGON vs sham NITESGON) versus participants' expected stimulation (active NITESGON vs sham NITESGON).

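### The blinding guess is asked only 28 days after the single session, and the stated blinding and adverse-event tests name only active and sham, leaving the anaesthesia and C5/C6 arms without a stated comparison

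*Protocol article*

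**What the plan says.** All references are to the protocol article.

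- **Timing.** Secondary outcome measures (2.7.2) states: "At the end of the experiment (T2), subjects will be asked if they thought they were assigned to the control or active group". Table 1 likewise marks blinding at T2 only. The same section places the adverse-event exit questionnaire, which covers tingling, itching and burning, at the end of T0. No guess is asked then.
- **Exposure and population.** Study procedure (2.5) describes "Administering one session of 1.5-mA active" or control stimulation, paired with the word task. Recruitment and screening (2.4) requires amnestic MCI with "Montreal Cognitive Assessment between 18 and 25".
- **Arms.** Study design (2.3): "One group will receive active NITESGON, while the three groups will be control groups". It also says that "all subjects and the investigator testing the endpoint measures will be blinded to the type of intervention". The three controls are there to show that the effect is real, depends on the site and is not produced by sensation. The primary hypothesis (2.1) sets active against the control groups, in the plural.
- **Current.** Intervention (2.6) gives the anaesthesia and C5/C6 arms the same current as the active arm.
- **Tests.** Statistical analysis (2.10) gives a chi-square for blinding, "comparing actual stimulation (active NITESGON vs sham NITESGON) versus participants' expected stimulation", with the guess also coded as active or sham. For adverse events: "A comparison will be conducted between the active and sham group using a one-way ANOVA".

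**The concern.** There are three separate weaknesses.

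**Timing.** A guess taken four weeks after a single session has two competing explanations besides sensation. Participants may no longer recall what the session felt like, which pulls guesses towards chance. They may also judge their allocation from how the recall tests went, which makes a working treatment look like failed blinding. The Discussion expects participants to do significantly worse on the learned words at 7 days, and Statistical analysis expects large behavioural effects, so neither explanation is far-fetched here.

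**Coverage.** The anaesthesia and C5/C6 arms are what allow the trial to say more than active beats sham. If participants in one of them could tell that they were controls, expectation could contribute to that contrast. No stated test would examine this. The same two arms are outside the stated adverse-event comparison.

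**Coding.** Participants are asked to choose between control and active, but the analysis codes active and sham. A C5/C6 participant receives real current and is nevertheless a control, so the two codings do not correspond.

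**Working it through.** **Inputs from the protocol article.** Four arms of 25, and dropout of no more than 20% (Sample size, 2.9). The article gives no figure for the blinding test, so there is none to reproduce.

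**Arm count.** 2 arms × 25 = 50 of 100 participants have no stated blinding or adverse-event comparison.

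**Numbers at T2.** 100 × (1 − 0.20) = 80, or 20 per arm if losses are even. Results below are for 25 and 20 per arm.

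**Power of the stated active-versus-sham test.** Let a and b be the numbers guessing active in two arms of size n. The Pearson statistic is

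X² = 2n[a(n − b) − b(n − a)]² / [n² (a + b)(2n − a − b)],

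significant if X² ≥ 3.84. Power is the sum of Bin(a; n, p₁) × Bin(b; n, p₂) over all significant pairs. The two-sided 0.05 level and all guess rates are assumptions.

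| Guess active: active arm / sham arm | Power, 25 per arm | Power, 20 per arm |
|---|---|---|
| 60% / 40% | 34% | 22% |
| 65% / 35% | 62% | 45% |
| 70% / 30% | 86% | 71% |
| 80% / 20% | 99.7% | 98% |

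The smallest symmetric difference found with 80% power is about 37 percentage points at 25 per arm and 44 at 20 per arm.

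**Illustration 1: fading memory.** Suppose a share u knows the allocation at the session, a share q of those has lost that knowledge by T2, and everyone else guesses at random. Then p = 0.5 ± u(1 − q)/2. With u = 0.6:

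- q = 0: 80% against 20%, power 99.7% / 98% (25 / 20 per arm).
- q = 0.25: 0.5 ± 0.225, or 72.5% against 27.5%, power 93% / 82%.
- q = 0.5: 0.5 ± 0.15, or 65% against 35%, power 62% / 45%.
- q = 0.75: 0.5 ± 0.075, or 57.5% against 42.5%, power 22% / 14%.

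**Illustration 2: guessing from performance.** Suppose blinding is perfect, but people with above-median recall guess active. With a true effect d, p = Φ(d/2) in the active arm and 1 − p in sham.

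- d = 0.8: Φ(0.4) = 0.655 against 0.345; the test is significant 65% / 48% of the time.
- d = 0.5: Φ(0.25) = 0.599 against 0.401; 33% / 22%.
- d = 0.8, with half the participants guessing this way and half at random: 0.5 + 0.5 × 0.155 = 0.578 against 0.422; 23% / 15%.

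A null result at T2 can therefore follow from forgetting, and a significant one from efficacy. How often depends on shares that the article does not give.

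**Coding, side by side.** If the chi-square uses only the active and sham arms, two arms are untested. If the two other stimulated arms are pooled as active, 75 participants are set against 25, and a C5/C6 participant who correctly answers control is counted as wrong. Neither reading gives a result for each control arm.

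**The case against.** The case for the plan is substantial.

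- **The T2 guess has a purpose.** It covers the whole blinded follow-up, including both delayed recall tests. Asking at T0 could make participants think about allocation before T1. This stands as a reason to keep T2 and as a cost of adding T0.
- **A reader might infer that the check cannot show whether blinding held.** That goes too far: unblinding of 80% against 20% that persists to T2 would be detected with 98% power or more.
- **A reader might infer that half the participants are left out of data collection.** They are not. The guess and the exit questionnaire are not restricted to particular arms, and Data management (2.11) promises summary statistics on all variables. The gap is in the named tests. Further analysis detail may sit in an analysis plan not shown, but the article does fix a two-group comparison for adverse events and names only two conditions for blinding.
- **The blinding wording is open.** The Abstract describes both other stimulated arms as active NITESGON, so pooling them is a possible reading. It does not help, as shown in the working.
- **A reader might infer that the anaesthesia and C5/C6 arms are the most open to unblinding.** The article does not support this. The C5/C6 placement is meant to reproduce the sensation, and each participant experiences one condition only. Sham, with its early ramp-down, may differ more.
- **A reader might infer that ANOVA is wrong for the adverse-event questionnaire.** That depends on its scoring, which is not shown.
- **Forgetting of the session is not documented.** The article describes loss of learned material. Memory of the stimulation itself may behave differently.

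**Conclusion.** The point holds in a limited form. The timing makes the guess harder to interpret but not uninformative. The firmer part is coverage: 50 of 100 participants are in arms with no stated blinding or adverse-event comparison, although those arms support the specificity claim. The mismatch between answer options and analysis coding is plain from the text.

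The arm count and timing come directly from the article. The power figures rest on an assumed two-sided 0.05 level and assumed guess rates; the two illustrations also assume the share forgetting, the guessing rule and the effect size. They show direction and possible size and are not predictions. Nothing here shows that blinding will fail or that the efficacy contrasts are invalid, since the guess does not enter the stated efficacy model.

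**What to change.** 1. **Analyse all four arms.** Tabulate guesses by arm and compare active with each control separately. Do the same for adverse events. This uses data already collected and costs only a change of wording. With 20 to 25 per arm, report proportions with confidence intervals, because a non-significant test leaves room for sizeable differences.
2. **Align the coding.** Use the same categories in the question and the analysis: control, active, don't know. State that the anaesthesia and C5/C6 arms count as control.
3. **Ask earlier as well.** Add the same question to the end of the T0 exit questionnaire and keep T2 as a repeat. The T0 answer precedes any delayed recall test, and the change from T0 to T2 shows how far guesses moved during follow-up. The cost is one item on an existing form. The downside is that it may prompt thoughts about allocation before T1. Asking it identically in every arm makes this less likely to differ between groups but does not remove it.

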### Safety

2.8

Transcutaneous electrical stimulation (tES) is a method that has been used in various clinical populations, including pain, Parkinson's disease, movement disorders, motor strike, aphasia, multiple sclerosis, epilepsy, disorders of consciousness, Alzheimer's disease, tinnitus, depression, schizophrenia, substance abuse, addiction, and craving [22]. Based on a previous review, there is currently no evidence of irreversible injury produced by conventional tES protocols using a wide range of stimulation parameters (≤40 min, ≤ 4 mA, ≤ 7.2 C) [23]. Furthermore, most adverse effects are mild and disappear soon after stimulation [24]. Another paper that summarizes 567 tES sessions over motor and non-motor cortical areas (occipital, temporal, parietal) revealed that according to the present safety guidelines, tES is associated with relatively minor adverse effects (including headache, itching or tingling sensation) in healthy humans and individuals with various neurological disorders [25]. To date, no significant differences in side effects have been observed after receiving active NITESGON compared to sham NITESGON [15,16,26].

### Sample size

2.9

The study is designed to give us adequate power to detect clinically meaningful differences between the groups. We plan to oversample to a target sample size of 25 subjects per group, with an overall sample of 100 subjects, to assure that our power to detect effects is maintained.

Nineteen individuals per group (total n = 76) would offer us a power of 90% to detect the difference between groups using Cohen's d estimation of a medium effect size (0.20). A sample size of 76 would allow us to see a medium effect size, however the trial is longitudinal which could increase its drop-out rate. Although we do not expect attrition to be large, we expect a dropout rate of no more than 20%. Therefore, an overall sample of 100 subjects will assure enough power to accommodate for the expected drop-out rate.

An intention-to-treat and per-protocol analysis will be performed. For the intention-to-treat analysis, the patient must successfully complete T0 and T1 assessments. For missing observations, the LOCF approach will be used. Exclusion from the population will be finalized prior to database lock in a blinded manner.

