### Statistical analysis

2.10

For our calculations, we will use the normal distribution assumption, which we will test using a normal plot and goodness of fit test. If violations are found, non-parametric tests or transformations will be utilized. Variance equivalence will be tested using the F-test. Our protocol is designed to assure sample independence, and adherence will be closely monitored. Before beginning the main statistical analyses, screening variable levels (e.g., age, sex, education, disease onset, mood) across groups will first be considered to assess group equivalence. If the groups are not balanced on any baseline characteristics, these factors will be considered as co-variate in later multivariate regressions.

The efficacy of NITESGON will be assessed on word recall by testing its effect on the mean change over time relative to the control groups. Memory task performance will be analyzed over time at baseline, and 7 and 28 days after NITESGON, and across groups. Statistically, these tests will be single degree-of-freedom interaction contrasts from a general mixed linear model containing both within- and between-subject variance components. All tests will be based on directional hypotheses in favor of improvements due to NITESGON on the behavioral assessment. We expect large behavioral effects based on our previous studies in control and patient populations.

*EEG.* sLORETA statistical contrast maps between pre and post NITESGON will be calculated for the sham and active groups through multiple voxel-by-voxel comparisons in a logarithm of F-ratio [27]. Statistical analysis is based on estimating, via randomization, the empirical probability distribution for the max-statistic under the null hypothesis comparisons [28]. This methodology corrects for multiple testing (i.e., for the collection of tests performed for all voxels and for all frequency bands). Due to the non-parametric nature of the method, its validity does not rely on any assumption of Gaussianity [28]. A comparison will be made between the contrast map for the active and sham group. The significance threshold is based on a permutation test with 5000 permutations. In addition, the statistical contrast map (pre-post) will be correlated with the difference on in memory improvement.

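### The stated 90% power for a medium Cohen's d of 0.20 with 19 per group is wrong as written, and the total of 76 fits a different test from the planned contrasts

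*Protocol article*

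**What the plan says.** Section 2.9 (Sample size) of the protocol article gives one power statement. It says that 19 participants in each arm, 76 overall, "would offer us a power of 90% to detect the difference between groups using Cohen's d estimation of a medium effect size (0.20"). It then allows for at most 20% dropout and sets the target at 25 per group, 100 in all. It names no alpha, sidedness, test or within-subject correlation.

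Section 2.10 (Statistical analysis) describes the efficacy analysis as "testing its effect on the mean change over time relative to the control groups", with baseline, day 7 and day 28 in the model. It says that "these tests will be single degree-of-freedom interaction contrasts from a general mixed linear model". On direction: "All tests will be based on directional hypotheses in favor of improvements due to NITESGON on the behavioral assessment". On size: "We expect large behavioral effects based on our previous studies in control and patient populations".

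The Background reports the group's earlier trial in 30 older adults, active against sham, with eta-squared of .21 at day 7 and .14 at day 28.

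**The concern.** Three things do not fit together. First, two groups of 19 are far too few to detect a standardised difference of 0.20 with 90% power. Second, 0.20 is the conventional small value on the d scale, yet it is called medium, while section 2.10 expects large effects. Third, 76 looks like the output of an omnibus repeated-measures calculation, which is not the test that section 2.10 plans.

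This sentence is the article's only quantitative justification of the sample size. A reader who relies on it could take a null result as good evidence against a small or medium benefit, when the planned contrasts would usually miss a small one and would often miss a medium one.

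**Working it through.** **Inputs from the article.** Four equal groups; 19 per group for power; 25 per group randomised; at most 20% dropout; effect 0.20; three time points; single-df directional contrasts; prior eta-squared .21 and .14.

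**Assumptions, not in the article.** Alpha 0.05; within-subject correlation ρ equal across visits, 0.5 or varied as shown. One-sided and two-sided results are both given.

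**1. The stated figure, read as written.** Noncentral t with noncentrality d/√(1/n₁ + 1/n₂) and n₁ + n₂ − 2 df, d in SDs of the change score:

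| Contrast, d = 0.20 | Noncentrality | One-sided | Two-sided |
|---|---|---|---|
| Active v one control (19 v 19) | 0.20 × √9.5 = 0.62 | 14.9% | 9.2% |
| Active v pooled controls (19 v 57) | 0.20 × √14.25 = 0.75 | 18.5% | 11.6% |

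A pairwise d of 0.20 would need 429 per group (one-sided) or about 527 (two-sided) for 90% power.

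**2. Could the correlation rescue it?** Put d on the raw-score scale. A single-visit change has variance 2(1 − ρ). The average of both follow-ups minus baseline has variance (1 + ρ)/2 + 1 − 2ρ = 1.5(1 − ρ). Dividing 0.20 by the square root of these and letting ρ run from 0 to 0.9:
- lowest: 7% (ρ = 0, one control, single visit, two-sided);
- highest: 61% (ρ = 0.9, pooled controls, follow-up average, one-sided).

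No combination comes near 90%.

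**3. A calculation that does give 76.** Read 0.20 as Cohen's f for the group-by-time interaction with k = 4, m = 3, ρ = 0.5. Then λ = f²·N·m/(1 − ρ), with (k − 1)(m − 1) = 6 and (N − k)(m − 1) df.
- N = 76: λ = 0.04 × 76 × 3/0.5 = 18.24, df 6 and 144, power 90.1%.
- N = 72: power 88.1%.

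76 is the smallest N that reaches 90%. Other readings of f = 0.20 at N = 76 fail: one-way ANOVA 26%, between-groups repeated measures 39%, interaction with two time points 82%.

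**4. What that f would mean.** If active differs by a from all three controls, equally at both follow-ups, then f² = (3/16)(2/9)a² = a²/24. Setting this to 0.04 gives a = √0.96 = 0.98 raw SD. With 19 per group and ρ = 0.5, a difference of that size has about 99% power in the pooled single-df contrast (follow-up average). Against one control it has 96% one-sided or 92% two-sided on the follow-up average, and 91% or 84% at a single visit.

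**5. Power at the earlier effects.** For two equal groups d = 2√(η²/(1 − η²)): .21 gives 1.03 and .14 gives 0.81. Twenty per group remain after 20% dropout (25 × 0.80). These between-group values are treated as if they were on the contrast's scale.

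| Prior effect | One control, 20 v 20 (one-/two-sided) | Pooled, 20 v 60 (one-/two-sided) |
|---|---|---|
| Day 7, d ≈ 1.03 | 94% / 89% | 99% / 98% |
| Day 28, d ≈ 0.81 | 80% / 70% | 93% / 87% |

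**6. Detectable effect at 90% power, 80 evaluable.**

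| Contrast | One-sided | Two-sided |
|---|---|---|
| One control, change-score SD | 0.94 | 1.05 |
| Pooled controls, change-score SD | 0.76 | 0.85 |
| One control, follow-up average, raw SD, ρ = 0.5 (× √0.75) | 0.82 | 0.91 |
| One control, follow-up average, raw SD, ρ = 0.7 (× √0.45) | 0.63 | 0.71 |

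For comparison, a change-score d of 0.5, the conventional medium value, has 46% or 34% power against one control and 61% or 48% against pooled controls.

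**7. Dropout.** 76/(1 − 0.20) = 95, and 100 × 0.80 = 80, which is at least 76. This step is sound.

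**The case against.** The case for the plan is that the sentence is only mislabelled. If 0.20 was a Cohen's f, the calculation is internally correct, and the effect it implies (0.98 SD under the pattern in step 4) agrees with the large effects that section 2.10 expects. The single-df contrasts would then have good power. This stands as a defence of the sample size. It does not defend the sentence, which names d and attaches 90% to it. The f reading is also an inference: the match at 76 is exact, but the article states neither the test nor the correlation of 0.5.

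It can also be said that pairwise figures are too harsh. That is fair. The article compares active with the control groups and does not say whether each control is tested separately or all are pooled. The reasons it gives for having three controls make separate tests plausible but do not settle it. A reader might therefore infer that success means beating all three controls, or that the trial is powered only for effects near 1 SD. The documents do not support either. No all-controls success rule is stated, and the detectable effect in step 6 runs from 0.63 to 1.05 depending on contrast, SD scale, correlation and sidedness.

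**Conclusion.** The power statement is wrong as written and should be corrected. For d = 0.20 and 19 per group, power on the change-score scale is about 9% to 15% against one control and 12% to 18% against pooled controls; with raw-score SDs it is at most about 61%, even at a correlation of 0.9. These figures rest on an assumed alpha of 0.05. The medium label conflicts with the metric, and the calculation that 76 most plausibly came from does not power the contrasts in section 2.10.

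A reader might go on to conclude that the trial is too small. That does not follow. At the day-7 prior effect, power with 20 per group is about 90% or better, one control or pooled. At the day-28 effect it is 70% to 80% against one control and 87% to 93% pooled. What is established is a false headline figure and an unnamed contrast, not an inadequate trial.

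**What to change.** Keep 100 participants. In section 2.9:

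- Delete the reference to Cohen's d, the word medium with its 0.20, the 90% claim attached to them, and the next sentence's statement that 76 suffices for a medium effect.
- Name the contrast being powered (each control or pooled; single visit or follow-up average), with alpha, sidedness, the SD scale and the assumed within-subject correlation.
- State the detectable effect for that contrast with 80 evaluable participants, from the table in step 6, and make the description of its size agree with section 2.10.
- If the omnibus calculation is kept, label it as Cohen's f = 0.20 with its correlation of 0.5, and say that it does not power the primary contrasts.

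The cost is wording only. Sample size, design and conduct do not change, but the stated figure becomes less favourable.

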### Outcome assessment

2.7

A variety of measures are included at the T0, T1, and T2 evaluations. The primary outcome measure is improvement in memory recall. Recall will be assessed using the word-association task during the learning phase at visit one (T0), 7 (T1) and 28 (T2) days after learning during NITESGON.

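### The set labelled intention-to-treat is a T1-completer set, and no analysis of all randomised participants is planned

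*Protocol article*

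**What the plan says.** All references are to the protocol article.

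- **Analysis set (2.9 Sample size).** An intention-to-treat and a per-protocol analysis are planned. The entry condition for the first is: "For the intention-to-treat analysis, the patient must successfully complete T0 and T1 assessments".
- **Missing data and exclusions (2.9).** "For missing observations, the LOCF approach will be used", and "Exclusion from the population will be finalized prior to database lock in a blinded manner".
- **Dropout (2.9).** "we expect a dropout rate of no more than 20" per cent. This covers the whole longitudinal trial.
- **Randomisation (2.3 Study design).** "Subjects will be randomized after screening evaluation and will be assigned to receive one of the four possible types of NITESGON".
- **Timing of T0 (2.5 Study procedure).** "Behavioral assessments after each of the three blocks of studying the word associations". Current is applied during each study phase (2.6 Intervention).
- **Timing of T1 and T2 (2.5).** "Behavioral assessments at seven (T1) and 28 (T2) days after NITESGON".
- **Primary outcome (2.7 Outcome assessment).** "Recall will be assessed using the word-association task during the learning phase at visit one (T0), 7 (T1) and 28 (T2) days after learning".
- **Primary analysis (2.10 Statistical analysis).** A mixed linear model with group-by-time contrasts over baseline, day 7 and day 28.

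**The concern.** Intention-to-treat means that everyone randomised is compared in the group to which they were assigned. Here membership depends on having a day-7 outcome value, which is obtained a week after treatment. Whether a person with aMCI returns and completes that test could depend on how the session felt, on frustration with the task, or on memory itself.

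Two kinds of participant are lost: those who leave before day 7, and those who miss day 7 but attend day 28 and so have a valid primary outcome value. If loss differs between arms and is related to recall, the groups compared are no longer the groups randomised. A difference between them could then imitate a treatment effect or hide one. The label tells readers that this protection is in place when it is not.

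**Working it through.** **1. Order of events.** Screening, randomisation, stimulated study blocks with a recall test after each (T0), day 7 (T1), day 28 (T2). T0 recall and T1 recall both come after randomisation and after stimulation has begun, so both entry conditions are post-randomisation events.

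**2. Who stays and who goes.**

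| Recall results available | In the set as written? |
|---|---|
| T0, T1, T2 | Yes |
| T0, T1 | Yes, T2 filled by LOCF |
| T0, T2 | No, although a day-28 outcome exists |
| T0 only | No |
| None | No |

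Because T1 is required, LOCF can in effect only carry T1 recall to T2.

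**3. The plan's own numbers.** The 76 participants are reproduced by a group-by-time interaction test with 4 groups and 3 time points, reading the stated 0.20 as Cohen's f and assuming alpha 0.05, within-person correlation 0.5 and sphericity. Power is 0.901 at N = 76. For 20% dropout, 19/0.8 = 23.75, so 24 per group; the planned 25 covers this.

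**4. Ceiling on exclusions.** If the full 20% were lost before T1, 0.20 × 100 = 20 would be excluded. That leaves 25 × 0.8 = 20 per group, still at least 19. The problem is comparability, not power.

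**5. Bias in T1 level, no true effect.** Let a proportion p of an arm be lost, with those lost scoring D SD below those retained. With the full-arm mean set to 0:

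(1 − p)m + p(m − D) = 0, so the retained mean is m = pD.

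The bias in the contrast is therefore (p₁ − p₂)D, where p₁ and p₂ are the losses in the two arms and D is the same in both.

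| Loss, arm 1 vs arm 2 | D = 0.5 | D = 1.0 |
|---|---|---|
| 20% vs 20% | 0 | 0 |
| 20% vs 10% | 0.05 SD | 0.10 SD |
| 30% vs 10% | 0.10 SD | 0.20 SD |

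The loss rates and D are assumptions; the article gives neither by arm.

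**6. Extreme case.** Suppose the lowest 20% of T1 recallers are lost in one arm only (5 of 25) and none in the other. For normal scores the retained mean rises by φ(z₀.₂₀)/(1 − 0.20) = 0.280/0.8 = 0.35 SD in T1 level. The planned contrast concerns change over time, and those lost also leave the T0 mean. With equal variances and an assumed T0–T1 correlation of 0.5, the T0 mean rises by 0.5 × 0.35 = 0.175 SD. The bias in change from T0 is then 0.35 − 0.175 = 0.175 SD.

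**The case against.** The strongest defence is that harmful loss is unlikely. Treatment is one session of 3 × 250 s, participants and endpoint assessors are blinded, section 2.9 does not expect large attrition, and section 2.8 reports no significant difference in side effects between active and sham to date. This stands as a reason to expect any bias to be modest. It does not make the label correct. Blinded exclusion prevents biased decisions about individuals, but it does not make attendance on day 7 independent of the assigned treatment.

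It could also be said that analysis sets belong in a fuller plan. But this is a rule that the article states, not a detail it leaves open.

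A reader might infer three stronger things that the article does not support:

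- **That this is a completer analysis throughout.** It is not: people with T1 but no T2 stay in.
- **That 20 of 100 will be removed.** The 20% is an upper allowance for the whole trial, and the article does not say how loss divides around day 7.
- **That a 0.35 SD bias should be set against a planned effect of 0.8 to 1.0 SD.** The first figure is a shift in one arm's level under extreme selection, not bias in the planned change contrast. The second is not a planning value: it converts the earlier study's η² of .14 and .21 (section 1), since 2√(.14/.86) ≈ 0.81 and 2√(.21/.79) ≈ 1.03. The value stated in section 2.9 is 0.20.

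**Conclusion.** The rule is wrong as written. The set is a T1-completer, or modified intention-to-treat, set, and the article describes no analysis of all randomised participants. The mislabelling is certain; material bias is not shown. Bias needs loss before T1 that differs by arm, in amount or in the deficit of those lost, and that is related to recall.

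Under the assumptions above, bias in T1 level is 0.05 to 0.10 SD for 20% versus 10% loss. In the extreme one-arm case it is 0.35 SD in level, or about 0.175 SD in change from T0 at a correlation of 0.5. It is zero when loss and deficit match across arms. The planned mixed model can use incomplete records, so the analysis does not need the restriction.

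**What to change.** 1. Define intention-to-treat as all randomised participants in their assigned group, analysed in the planned mixed linear model with every available T0, T1 and T2 result.
2. Delete the LOCF rule for this analysis and let the likelihood-based model handle missed visits. The two changes must go together. If the T1 condition went but LOCF stayed, end-of-learning T0 recall would be carried to days 7 and 28, and early dropouts would be scored as having forgotten nothing.
3. Keep completion of T0 and T1 only in the per-protocol definition, or relabel that set modified intention-to-treat and make it a secondary analysis.
4. Optionally, add one sensitivity analysis with an unfavourable assumption for participants who have neither a T1 nor a T2 result.

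The cost is a rewording of the analysis-set and missing-data sentences in section 2.9 and a little extra analysis. No new data are needed.
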